**Figure 1 figure1:**
[figure not shown]
The Face-Forward-Web conceptual model.

This study aims to (1) develop *Face-Forward-Web* with the aid of live video focus groups with adults with COP and (2) optimize *Face-Forward-Web* and our study protocol through beta testing (n=up to 10) to refine the intervention followed by a feasibility trial (n=up to 20). The results will inform future efficacy research, evaluating *Face-Forward-Web* versus an active control web platform in improving pain interference, depression, and anxiety.

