### The Face-Forward-Web Intervention

*Face-Forward-Web* consists of 5 sessions (Table 1), which teach relaxation (eg, body scan, deep breathing), mindfulness, and cognitive-behavioral skills (eg, adaptive thinking, reducing negative affective reactivity). The content is consistent with *GetActive* [44] and adapted to the unique needs of people with COP and for delivery via the web platform. Due to the individual/asynchronous format of *Face-Forward-Web*, we were able to condense the *GetActive* content into 5 sessions, which may maximize feasibility and engagement (to be tested in the proposed studies). Each session consists of a combination of short (~5-10 minutes) videos conveying educational content and skill delivery. Each session ends with an interactive quiz covering the session’s content to gauge comprehension and facilitate material absorption, which can be an effective intervention element for people with chronic pain [51]. Audio and video clips will be available to guide participants through their daily home practice. Once invited by a research assistant, participants will log in and access the first session’s materials. Contingent on completion of the interactive quiz at the end of each session, access to the subsequent session will be granted in the following week. Participants will be free to review and practice all the skills and materials from the completed sessions until the 3-month follow-up assessment and will be encouraged to use the platform for daily practice. The platform will be easily accessible across multiple interfaces such as a website and mobile app through any internet-enabled device (eg, smartphone, tablet, computer). We will track participants’ homework completion and platform activity. To encourage retention, we will text reminders about the sessions and home practice through the Health Insurance Portability and Accountability Act–compliant texting service, as previously successfully implemented by our group and deemed useful by participants [52].

**Table 1 table1:** Face-Forward-Web session topics and examples of content.

Session	*Face-Forward-Web* topic	Skills and examples of content/videos
1	Taking charge of orofacial pain	Orofacial “Pain alarm” (reactions to COP^a^) Debunking myths about COP Downward and upward spirals (COP is associated with thoughts, feelings, and behaviors that can be maladaptive or adaptive) Deep breathing
2	Managing emotional challenges in orofacial pain	Mindfulness Body scan

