3	Working with negative thoughts	Identifying NATs^b^ Checking NATs Challenging NATs
4	Not letting orofacial pain get the best of us	Acceptance Using Face-Forward-Web skills to reengage in activities (eg, daily, recreational, social, family, work-related)
5	Facing forward: “Rolling” with orofacial pain and staying resilient	Mindfulness of discomfort and pain Review all skills Create personalized plan

^a^COP: chronic orofacial pain.

^b^NAT: negative automatic thought.

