### Treatment Delivery and Protocol Adherence

Participants will continue their usual care as determined by their medical providers (eg, medication, occlusal splits and adjustments, physical therapy). We will determine fidelity to *Face-Forward-Web* via a user experience software such as Google Analytics [53]. This will enable us to track participants’ frequency and time spent on each of the web platform’s pages and clicks on exercises and quizzes and evaluate participation, even on partially completed sessions, thereby increasing the accuracy of attendance evaluation.

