#### Phase 2: Beta and Feasibility Testing With Exit Interviews

We will use frequency and proportions to assess the feasibility of the recruitment and retention procedures. We will determine treatment satisfaction and credibility by the proportion of participants who score above the scale midpoint in the User Experience Questionnaire [65] and Credibility and Expectancy Questionnaire [66], respectively. See Table 2 for further details on the feasibility, credibility, and acceptability benchmarks, consistent with other established feasibility work [67-69]. We will analyze qualitative data from the exit interviews by using the same procedures described in phase 1.

**Table 2 table2:** Feasibility benchmarks.

Outcome	Acceptable	Excellent
Credibility and expectancy	>70% of the participants with score over scale midpoint.	>75% of the participants with score over scale midpoint.
User experience	>70% of the participants with score over scale midpoint.	>75% of the participants with score over scale midpoint.
Feasibility of recruitment	>70% of eligible participants agree to participate.	At least 80% of eligible participants agree to participate.
Acceptability of treatment	>70% of the participants attend 3 out of 5 sessions.	>80% of the participants attend 3 out of 5 sessions.
Adherence to homework	>70% of the participants practice >1 skill on 3 d/wk.	>80% of participants practice >1 skill on 3 d/wk.
Feasibility of assessments	>70% of the participants have no measures fully missing.	>90% of the participants have no measures fully missing.
Adverse events	Minimal	None

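### Because sessions unlock in order, Table 2 can grade acceptability Excellent when nobody goes beyond session 3, while the Abstract's rule scores the same data 0%

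*Protocol article*

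**What the plan says.** The section on the Face-Forward-Web intervention describes five sessions taken in a fixed order. Once invited, "participants will log in and access the first session’s materials". After that, "Contingent on completion of the interactive quiz at the end of each session, access to the subsequent session will be granted in the following week". The same section says that condensing the parent programme into five sessions may help feasibility and engagement, and that this study will test it.

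Table 1 places deep breathing in session 1, mindfulness and the body scan in session 2, and negative thoughts in session 3. Session 4 covers acceptance and "Using Face-Forward-Web skills to reengage in activities". Session 5 covers mindfulness of pain, a review of all skills and a personal plan.

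Table 2 (Data Analysis, Phase 2) grades acceptability of treatment. The Excellent tier is ">80% of the participants attend 3 out of 5 sessions". The Acceptable tier has the same wording with 70% in place of 80%. The Abstract, listing the primary outcomes, instead asks that at least 70% of participants complete a minimum of four sessions (its wording is four or five).

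On measurement, Treatment Delivery and Protocol Adherence says that platform tracking will allow staff to "evaluate participation, even on partially completed sessions".

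**The concern.** An attendance count of three out of five suits a programme in which someone can miss a session and come back for a later one. Here a missed quiz ends progress, so the count is really a stopping point. A threshold of three says nothing about whether anyone went further, and the higher tier raises only the share of people, not how far they get.

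The content after session 3 matters to the study's stated purpose. The Introduction describes pain interference as activity limitation due to pain, and the planned efficacy trial is to compare the platform with an active control "in improving pain interference, depression, and anxiety". The only listed session naming activity re-engagement lies beyond the benchmark. So does the part of the five-session format whose feasibility the study says it will test. A top grade on a primary outcome could therefore be carried into the efficacy trial without showing that participants stay to the later sessions.

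**Working it through.** The plan gives no derivation for this benchmark, so there is no figure to reproduce. The check is an enumeration and a count.

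**Inputs.** Five sessions, starting at session 1, each later one unlocked by the previous quiz (The Face-Forward-Web Intervention). Thresholds of more than 70% and more than 80% attending three of five (Table 2). At least four sessions completed by at least 70% (Abstract). Up to 20 participants (Study Design and Setting).

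**Step 1: possible attendance patterns.** With a locked sequence the sets of sessions attended are: none, {1}, {1,2}, {1,2,3}, {1,2,3,4} and {1,2,3,4,5}. The only three-session set is {1,2,3}. Without the lock there would be C(5,3) = 10 such sets, of which C(4,2) = 6 include session 4.

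**Step 2: smallest number of participants meeting each tier.**

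| n | more than 70% | more than 80% |
|---|---|---|
| 10 | 8 (80%) | 9 (90%) |
| 15 | 11 (73.3%) | 13 (86.7%) |
| 20 | 15 (75%) | 17 (85%) |

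Each count can be reached with nobody opening session 4.

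**Step 3: the same data under both definitions, n = 20.**

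| Pattern | Table 2: three or more sessions | Abstract: four or more sessions |
|---|---|---|
| 17 stop after session 3, 3 stop after session 2 | 17/20 = 85%, Excellent | 0/20 = 0%, not met |
| all 20 stop after session 3 | 20/20 = 100%, Excellent | 0/20 = 0%, not met |

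**Step 4: does another row of Table 2 catch this?** No. The homework row can be met with skills taught in sessions 1 to 3. The assessment row counts missing questionnaires. Credibility and user experience are questionnaire scores, and adverse events do not concern attendance.

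**Step 5: partial sessions.** Only the last session opened can be incomplete, since every earlier quiz must have been completed. If a partial session were scored as attended, someone with three sessions attended would have completed at least 3 − 1 = 2. Whether partial sessions score in this way is not stated, so this is an assumption and steps 1 to 4 do not use it.

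**The case against.** The strongest reply is that this is largely the conflict between the Abstract and Table 2. If the authors adopt the Abstract's rule, the gap closes, because under the lock four completed sessions must include session 4. That is right, and reconciling the two comes first. But if Table 2's count is kept, the gap remains in full.

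Four stronger readings are tempting, and the documents do not support them.

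- *Three of five always means sessions 1 to 3.* An attendance benchmark is naturally read as at least three, so people who go further also count. Sessions 1 to 3 are the minimum passing set.
- *Nobody need have completed more than two sessions.* The adherence section says tracking can assess participation in partial sessions and make attendance more accurate. That is equally compatible with separating partial from full attendance.
- *Session 4 is the essential component.* The conceptual model names pain catastrophizing, fear of pain and mindfulness as targets, not activity re-engagement. Table 1 lists examples of content only.
- *The study cannot detect drop-off.* Page, exercise and quiz tracking, module ratings and exit interviews would show it. The weakness lies in the graded benchmark, not in the data collected.

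It is also fair to say that 17 of 20 stopping at the same point is a constructed extreme, that the benchmarks are descriptive, and that no decision to proceed is tied to the Excellent tier. The article says its benchmarks follow established feasibility work, which is not available here. Even so, a customary threshold need not suit a locked sequence.

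**Conclusion.** The point holds in a limited form. Under sequential unlocking, Table 2's acceptability row can be met at both tiers by participants who stop after session 3. At n = 20 the extreme is 85% or even 100%, graded Excellent, with 0/20 reaching sessions 4 and 5, against 0% under the Abstract's definition. The example shows what the rule permits and is not a forecast of how participants will behave.

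The conclusion rests on the unlocking rule as written and on reading three of five as at least three. It needs no assumption about partial sessions or about which session matters most. The consequence is moderate: no test or decision rule is invalidated, but a primary outcome can be graded in opposite ways from the same data, and its top grade says nothing about the last two of the five sessions.

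**What to change.** 1. Reconcile Table 2 with the Abstract before phase 2 data are graded: one session count, stated as a minimum, and one verb (attend or complete).
2. Score acceptability from the quiz-completion record, and state that a partial session does not count as attended.
3. Add a Table 2 row for the share of participants completing session 4, and report the number completing each session in order.

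Making session 4 a condition of the Excellent tier is a possible alternative, but that is a debatable choice of threshold. The separate row gives the same information without it.

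The platform must already hold quiz completion in order to unlock sessions, so the work is table wording and one extra tabulation. The Results section says that as of August 2025 intervention content was only starting to be created, so on that timeline the rule could be settled before phase 2 data are graded. The downside is that the acceptability figure may look less favourable.

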## Results

This study is funded by the National Institute of Dental and Craniofacial Research grant 1R21DE033502-01A1 to JG and [name]. Recruitment began in October 2024 for phase 1. Data collection for phase 1 was completed in March 2025. Primary data analysis for phase 1 is expected to conclude by fall 2025 and in 2026 for phase 2. As of August 2025, we have completed 4 planned focus groups with a total of 22 participants representing a variety of COP diagnoses, including temporomandibular joint dysfunction, trigeminal neuralgia, and burning mouth syndrome. The rapid data analysis is complete, and we are beginning thematic analysis. We are starting to create intervention content, informed by results from our focus groups. Once available, we will share the data and results in the Vivli global clinical research data sharing platform.

## Discussion

Pain interference and emotional distress are prevalent among people with COP [62] but are commonly neglected in current treatments [20,39]. Available psychosocial interventions such as cognitive behavioral therapy [21-28] and other behavioral programs [29-32] show promise in improving outcomes in individuals with COP [21-32] but are often not suitable for people with COP due to several limitations. Most notably, these interventions typically rely on verbal communication, which is often painful for this population due to facial pain symptoms, which can be exacerbated by talking. Additionally, such interventions can be associated with stigma and require extensive resources (eg, availability of a trained live clinician). Here, we describe a protocol to develop, test, and refine *Face-Forward-Web*, the first talk-free web-based intervention for adults with heterogeneous COP, tailored specifically to meet their needs and challenges. By teaching mind-body (eg, mindfulness, relaxation) and cognitive behavioral skills within a talk-free modality, this intervention holds potential to bypass barriers and address these commonly neglected needs [38].

We anticipate that the results of phase 1 will align with our preliminary work underscoring the need for a COP intervention that addresses psychosocial factors [20] and uses a web-based platform. We also anticipate findings to highlight specific elements of the intervention’s content, structure, and study procedures that can be tailored to maximize fit for this population’s needs. Assuming the successful integration of these findings, we hypothesize that phase 2 will demonstrate high levels of feasibility across domains (eg, user experience, acceptability, adherence) and no adverse events related to study participation.

We follow the NIH stage model [48] and prioritize establishing feasibility and iterative refinement of the intervention prior to efficacy testing. By integrating qualitative methods, our approach centers on participant needs and preferences, ensuring that the intervention is best positioned to support those impacted by COP. Once both phases are complete, these results will inform a future efficacy trial of *Face-Forward-Web* versus an active control platform.

Potential limitations should be considered. First, the study relies on participants’ self-reported diagnoses and symptoms. This limitation is partially mitigated by our recruitment methods, which include referrals from COP medical specialists and established advocacy groups. Second, our broad diagnostic inclusion criteria may reduce the specificity of the findings. However, our preliminary research suggests that individuals across diagnostic categories share more common needs than differences. This inclusive approach enhances the potential for generalizability to a broader population and may be considered a potential strength. Other strengths include the use of established feasibility benchmarks, validated measures, and following the NIH model for behavioral intervention development.

Our work has yielded a few lessons learned thus far. First, given our small budget, we have had to carefully prioritize spending and have chosen to focus on the remuneration of participants [70]. Additionally, for recruitment, we have found both professional networks (providers who treat COP) and community resources (Facial Pain Association) to be effective. However, meeting our goal of including the perspectives of diverse populations, including a variety of COP diagnoses, as well as racial, ethnic, and medically underserved areas [71] has required additional strategies such as direct engagement of referral providers.

In summary, this protocol describes the development, refinement, and feasibility testing of *Face-Forward-Web*, the first talk-free web platform for adults with heterogeneous COP, tailored specifically to their needs and challenges by using mixed methods. We will utilize the NIH stage model for behavioral intervention development [47,48], the Science of Behavioral Change framework [72], and a user-centered design process to maximize the intervention’s fit for this population’s needs [40,41]. Our results will establish feasibility and directly inform a subsequent efficacy trial.

## Appendix

Multimedia Appendix 1 SPIRIT (Standard Protocol Items: Recommendations for Interventional Trials) checklist.

Multimedia Appendix 2 Focus group interview script.

Multimedia Appendix 3 Peer review report by BMHO - Biobehavioral Medicine and Health Outcomes Study Section Risk, Prevention and Health Behavior Integrated Review Group (National Institutes of Health, USA).

## Abbreviations

COP: chronic orofacial pain
NIH: National Institutes of Health
REDCap: Research Electronic Data Capture
SPIRIT: Standard Protocol Items: Recommendations for Interventional Trials
